## Abstract

**Background:**

Low back pain affects approximately 80% of people at some stage in their lives. Exercise therapy is the most widely used nonsurgical intervention for low back pain in practice guidelines. Whole body vibration exercise is becoming increasingly popular for relieving musculoskeletal pain and improving health-related quality of life. However, the efficacy of whole body vibration exercise for low back pain is not without dispute. This study aims to estimate the effect of whole body vibration exercise for chronic low back pain.

**Methods/Design:**

We will conduct a prospective, single-blind, randomized controlled trial of 120 patients with chronic low back pain. Patients will be randomly assigned into an intervention group and a control group. The intervention group will participate in whole body vibration exercise twice a week for 3 months. The control group will receive general exercise twice a week for 3 months. Primary outcome measures will be the visual analog scale for pain, the Oswestry Disability Index and adverse events. The secondary outcome measures will include muscle strength and endurance of spine, trunk proprioception, transversus abdominis activation capacity, and quality of life. We will conduct intention-to-treat analysis if any participants withdraw from the trial.

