### Outcome measures

Primary outcome measures include the following:

1. Pain intensity, which will be assessed using the VAS. It is usually a horizontal line, 100 mm in length, which is marked with ‘no pain’ (score 0) and ‘unbearable pain’ (score 10) from the left to the right. The patient marks on the line the point that they feel represents their perception of their current state. The amount of pain that a patient feels ranges across a continuum from none to an extreme amount of pain [31].

2. Back function, which will be measured using the Oswestry Disability Index [32], an index that consists of ten sections related to activities of daily living commonly affected by low back pain. Each section is scored from 0 to 5 with higher values indicating more severe impact.

3. Adverse events associated with whole body vibration exercise, which will be reported.

Secondary outcome measures include:

1. Muscle strength and endurance of trunk, which will be tested using a Biodex 3 dynamometer (Biodex Medical Systems, New York, USA). Participants will perform ten maximum concentric contractions for trunk extensors and flexors at the angular velocities of 60°/s, 120°/s. The muscle endurance index is defined as the ratio of the work done during the last five contractions over the first five contractions. Main outcome parameters will be peak torque (Newton-meters), peak torque/ body weight, maximal power output (power) in Watts, work (work) in Joules [33].

2. Trunk proprioception, which will be assessed with a joint position matching test [24]. The subject’s trunk will be moved to reference position (flexion or extension), and maintained at the position for 3 s. Then the subjects will be asked to reproduce the reference position from the neutral position. The subject is instructed to stop a position when he or she thinks that the test position has been reached. The assessor records the position and angle. This sequence of events will be repeated three times, and these three measures were averaged for a score of repositioning error for the first pre-test. The large absolute error is considered as poor proprioceptive acuity.

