### Statistical analysis

The SPSS 17.0 and Microsoft Excel 2007 software will be used to perform statistical analyses. Data will be expressed as mean?±?standard deviation (SD). We will use two-way repeated measures analysis of variance (group?×?time) to compare the effect of WBV exercise group with the control group, including the primary and secondary outcomes. If subjects are lost to follow-up, an intention-to-treat analysis will be conducted. A T-test will be used to compare the changes in measures within groups when the analysis of variance reveals a significant difference. Statistical significance is a *P* less than 0.05.

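### Pain (VAS) and disability (ODI) are both primary and each is tested at 0.05 with no rule for combining them, so if either can carry the claim the false positive risk is about 7–10%, not 5%

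*Protocol article*

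**What the plan says.** The abstract of the protocol article names three primary outcomes: "Primary outcome measures will be the visual analog scale for pain, the Oswestry Disability Index and adverse events". The Outcome measures section lists the same three separately: "Pain intensity, which will be assessed using the VAS"; "Back function, which will be measured using the Oswestry Disability Index"; and "Adverse events associated with whole body vibration exercise, which will be reported". The first two are efficacy measures. The third is only to be reported, and no test suited to it is named.

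The Statistical analysis section plans a two-way repeated measures ANOVA (group by time) "to compare the effect of WBV exercise group with the control group, including the primary and secondary outcomes". Its decision rule is one sentence: "Statistical significance is a *P* less than 0.05". The article names no leading primary outcome, gives no split of alpha and no testing order, and does not say whether success needs one efficacy outcome or both.

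**The concern.** A 0.05 threshold controls the error of one test. With two primary efficacy outcomes there are two chances to cross it. Unless both must be significant, or the two share the 0.05 by a stated rule, the error rate attached to the trial's conclusion is higher than the threshold suggests.

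The Aim of the study section asks whether vibration exercise is more beneficial than general exercise. A significant result on pain alone, or on disability alone, could be offered as a yes. The Discussion in the abstract addresses the results to patients, medical staff and decision makers. These readers would take a primary result at P below 0.05 as carrying a 5% risk of error.

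**Working it through.** **Inputs from the protocol article**

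- Primary efficacy outcomes: 2, VAS and ODI (abstract; Outcome measures).
- Test: one group-by-time ANOVA per outcome (Statistical analysis).
- Threshold: 0.05 for each test (Statistical analysis). Sidedness is not stated; two-sided is assumed.
- Size: 120 patients, 1:1, so 60 per arm (Study design).
- Assessments: before intervention, 3 months and 6 months (Study design).

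**Assumed:** the correlation between the VAS and ODI test statistics. The article gives none, so the range 0 to 0.9 is shown.

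**Step 1. The article's own figure.** The only error rate stated is 0.05. The group-by-time interaction F test was simulated under no effect (60 per arm, 3 visits, compound symmetry, 20,000 runs per setting). The rejection rate for one outcome was 0.049 to 0.052. So 5% is right for each test.

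**Step 2. Two outcomes, independent tests.** The chance of at least one false positive is 1 − (1 − 0.05)² = 1 − 0.9025 = 0.0975, or 9.75%. Whatever the dependence, it cannot exceed 0.05 + 0.05 = 10%.

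**Step 3. Two outcomes, correlated tests.** With bivariate normal statistics, the chance is 1 − P(|Z₁| ≤ 1.96 and |Z₂| ≤ 1.96). The chance that both are falsely significant is 0.10 minus that figure. The simulated column uses the interaction F test from step 1.

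| Assumed correlation | At least one (normal) | At least one (simulated F test) | Both |
|---|---|---|---|
| 0 | 9.75% | 9.6% | 0.25% |
| 0.3 | 9.51% | 9.95% | 0.49% |
| 0.5 | 9.07% | 9.0% | 0.93% |
| 0.7 | 8.35% | 8.6% | 1.65% |
| 0.9 | 7.04% | 7.2% | 2.96% |

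The simulated values carry a standard error of about 0.2 percentage points (√(0.095 × 0.905 / 20,000) = 0.0021).

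**Step 4. Direction.** These figures count false positives in either direction. For false claims favouring vibration only, the chance is 4.9% if independent and 4.5% at correlation 0.5, against 2.5% for a single test. The relative inflation is much the same.

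**Step 5. After a correction.** With 0.025 for each outcome, the chance of at least one false positive when neither outcome has an effect is 1 − 0.975² = 4.94% if independent. It is 4.84%, 4.65%, 4.30% and 3.62% at correlations 0.3, 0.5, 0.7 and 0.9. Holm starts at the same 0.025, so it has the same error in that case.

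**Step 6. Cost in sensitivity.** The yardstick is a two-group comparison of means with 60 per arm analysed and 80% power. Both are assumptions; the article states no power. The normal approximation gives (z for alpha + 0.842) × √(2/60):

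- at 0.05: (1.960 + 0.842) × 0.1826 = 0.51 SD;
- at 0.025: (2.241 + 0.842) × 0.1826 = 0.56 SD.

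The exact t calculation gives 0.516 and 0.569 SD, so about 0.52 and 0.57.

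**The case against.** The strongest reply is that this is a condensed article, and that alpha sharing is commonly left to an analysis plan that is not shown. The sentence on significance can be read as a per-test convention, and the article never claims a family-wise 5%. Part of this stands: the list of primary outcomes is not itself an error, and if both outcomes had to be significant there would be no inflation (the last column in step 3 stays below 5%). But the article does more than stay silent. It fixes the threshold, "less than 0.05", for the primary and secondary outcomes alike, and anyone following that rule as written incurs the risk calculated above. The Discussion does mention reducing pain and improving function together, but as an expectation and not as a condition for success.

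Four stronger readings are tempting, and the document does not support them.

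- **Two follow-up visits add to the error.** They do not. The group-by-time test pools the visits into one test per outcome. The only follow-up tests described are within-group t-tests, made after a significant ANOVA.
- **The risk is 16–19%.** That requires a significant group main effect to count as success alongside the interaction. The article does not say so. Four fully independent tests would give 1 − 0.95⁴ = 18.5%, so the upper end is not attainable with positively correlated outcomes.
- **A definite number of false secondary findings can be predicted.** The section names several dynamometer parameters: "Main outcome parameters will be peak torque (Newton-meters), peak torque/ body weight, maximal power output (power) in Watts, work (work) in Joules". It does not say how they will be crossed with muscle group and speed for testing, so any total, such as about 31 secondary measures, is inferred. Testing secondary outcomes without adjustment is also common practice.
- **One visit must be made primary.** The multiplicity between VAS and ODI does not require this. Choosing 3 months would set aside the 6-month follow-up, which the Strengths and limitations section presents as a strength.

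**Conclusion.** The point holds in a limited form. Two primary efficacy outcomes are each tested at 0.05, with no statement of how they share it or whether both are needed. If either can support the claim of benefit, the chance of at least one false positive primary efficacy result is about 7–10%.

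This rests on two-sided testing, on one interaction test per outcome, and on an assumed correlation between 0 and 0.9. A single figure of about 9% would imply a correlation near 0.5, which the article does not give. Adverse events are left out because they are only reported. If they were also tested at 0.05, the independent figure would be 1 − 0.95³ = 14.3%.

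The trial remains interpretable. The rule should be settled before the data are seen, and the Trial status section says that recruitment is already underway.

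**What to change.** In the Statistical analysis section, keep the planned group-by-time test for VAS and for ODI, and add one rule that controls the overall two-sided 0.05 across them. Either of these will do:

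- **Holm:** test the smaller of the two P values at 0.025 and, if it is significant, the other at 0.05.
- **Fixed sequence:** test VAS at 0.05 and test ODI at 0.05 only if VAS is significant.

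If the sponsor in fact intends that both must be significant, one sentence saying so also removes the inflation.

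State that adverse events are reported descriptively outside this efficacy family, and that secondary outcomes are supportive.

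The change is one of wording; no visit, measurement or patient is added. Holm's first step raises the detectable difference from about 0.52 to 0.57 SD on the assumptions in step 6; dropout would raise both figures. A fixed sequence costs VAS nothing, but ODI cannot be claimed if VAS is not significant.

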**Discussion:**

Important features of this study include the randomization procedures, single-blind, large sample size, and a standardized protocol for whole body vibration in chronic low back pain. This study aims to determine whether whole body vibration exercise produces more beneficial effects than general exercise for chronic low back pain. Therefore, our results will be useful for patients with chronic low back pain as well as for medical staff and health-care decision makers.

**Trial registration:**

Chinese Clinical Trial Registry: ChiCTR-TRC-13003708.

## Background

Low back pain (LBP) is a major public health challenge all over the world [1,2]. The lifetime prevalence of LBP is shown to be 84%, and the prevalence of chronic LBP is about 23%, 11 to 12% of people are disabled by LBP [3]. Because of its high prevalence, LBP often leads to a large economic burden with regard to medical expenses and lost wages [4,5]. In the United States, statistics show that total direct and indirect costs for the treatment of LBP are estimated to be more than $100 billion each year [6,7].

Exercise therapy is recommended as an effective treatment for relieving pain and improving back function for patients with LBP by most clinical guidelines [3,8-11]. During the past decade, whole body vibration (WBV) exercise has become increasingly popular for relieving musculoskeletal pain and improving health-related quality of life [12,13]. In whole body vibration, the vibration signals are delivered through a vibratory platform or chair to expose a larger part of the body to the stimulation [14]. WBV exercise consists of standing statically or performing dynamic movements on an oscillating platform. Exercise training using vibratory platforms may be a complementary training to standard physical rehabilitation programs. WBV provides amplitude of displacement (ranging from 0.7 to 14 mm) and a mechanical oscillation of a specific frequency (ranging from 0.5 to 80 Hz) [15,16]. Several studies have demonstrated that whole body vibration exercise can reduce pain for women with fibromyalgia syndrome [17], young patients with musculoskeletal pain [18], and elderly patients with knee osteoarthritis [19].

At present, WBV exercise is being marketed as an intervention for patients with LBP [20-25]. There are two reasons WBV exercise may be useful for alleviating pain in patients with LBP. First, LBP is known to be associated with reduced abdominal and back extensor stabilization muscle activity [26]. It has been proposed that WBV may assist in reducing LBP by activating stretch reflexes and subsequently activating and strengthening the abdominal and back extensor stabilization muscles [23]. Second, LBP is known to be associated with paravertebral muscle spasm, and it has been suggested that WBV at frequencies below 20 Hz may reduce LBP by inducing muscle relaxation [27].

Whole body vibration exercise has a theoretical basis in treatment of LBP, as is evidenced by its clinical use. However, the efficacy of WBV exercise for low back pain is not without dispute. The results of several studies suggest that whole body vibration exercise relieves chronic back pain through a genuine analgesic effect [21-23]. On the other hand, some studies show that WBV exercise was not effective for patients with LBP [28,29], and WBV has even been considered harmful [30].

It is important to ensure that the determination of the effectiveness of WBV exercise for LBP is based on scientific evidence so as not to waste staff time and resources and to avoid unnecessary stress for patients with LBP and their families. Thus, we conduct a single-blind randomized controlled trial (RCT) to determine the effects of WBV for patients with LBP compared to general exercise.

## Methods/Design

### Aim of the study

We will perform an RCT involving whole body vibration exercise in patients with chronic low back pain in order to determine:

1) whether WBV exercise is effective for the treatment of chronic LBP,

2) whether WBV exercise produces more beneficial effects than general exercise for chronic LBP, and

3) adverse effects associated with whole body vibration.

### Study design

This is a single-blind randomized controlled trial comparing a WBV exercise with general exercise (Figure 1). A total of 120 patients with chronic LBP will be recruited and investigated from Shanghai Shangti Orthopedic Hospital and Shanghai University of Sport, Shanghai City, China.

**Figure 1 F1:**
[figure not shown]
Flow diagram showing whole body vibration exercise for patients with low back pain (LBP).

All participants, prior to initiation of the study, will accept a questionnaire asking for the following details: basic information (for example, age), past and present job status, medical history, pain (visual analog scale, VAS), back function (Oswestry Disability Index, ODI) and exercise habits (for example, frequency and time/session). Prior to inclusion, informed consent will be sought from all participants in the study.

The subjects will be allocated in a 1:1 ratio by computer-generated randomization if they meet the inclusion criteria. After randomization, patients with chronic LBP will be assigned to the control group (general exercise) or to the intervention group (WBV exercise). The total study period will be 6 months, which has a 3-month intervention and 3-month follow-up period with no intervention. The study will include assessments at the following time points: before intervention, at 3 months, and at 6 months.

### Participants

Inclusion criteria are:

1. age 18 to 60 years old,

2. pain for more than 3 months,

3. lack of abnormal sense and reflection of the lower extremity,

4. medication not expected to change during the study period, and

5. availability 3 times a week over a period of 3 months.

Exclusion criteria are:

Subjects who have any of the following conditions will be excluded:

1. undergone previous surgery, dislocation, fracture, rheumatoid arthritis, and ankylosing spondylitis;

2. severe cardiovascular, progressive neurological deficits, severe osteoporosis, or metabolic diseases;

3. low back pain caused by visceral disease;

4. VAS score (from 1 to 10) above 8;

5. inability to communicate in Chinese;

6. attended WBV exercise last 3 months;

7. pregnant or lactating.

8. uncontrolled hypertension; or

9. other illness, judged by the patient or study physician to make participation in this study inadvisable.

### Withdrawal criteria and management

Patients with chronic LBP will be allowed or be asked to withdraw from the study if:

1. The patient makes such a request.

2. The patient develops a serious disease, such as stroke or heart disease.

3. The patient has an adverse effects related to the WBV exercise.

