#### Control group

The participants in the control group will perform the same exercise protocol as the WBV group, but without vibration. The participants in the both groups will be asked to maintain their previous lifestyle and not take part in any other regular rehabilitation programs.

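### A vibration-related adverse effect is a ground for leaving the study, not only the exercise; only the WBV arm can meet it, so pain and disability outcomes may go missing in that arm alone

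*Protocol article*

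**What the plan says.** The section Withdrawal criteria and management opens its list with "Patients with chronic LBP will be allowed or be asked to withdraw from the study if". The list has three items: the patient's own request; serious disease ("The patient develops a serious disease, such as stroke or heart disease"); and "The patient has an adverse effects related to the WBV exercise". The third item gives no severity threshold, and there is no matching item for an adverse effect of the exercises themselves.

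On the comparator, the Control group section says: "The participants in the control group will perform the same exercise protocol as the WBV group, but without vibration".

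On timing, the Study design section says: "The study will include assessments at the following time points: before intervention, at 3 months, and at 6 months". The intervention lasts 3 months, so the first measurement after baseline falls at its end.

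On outcomes, the third primary outcome is "Adverse events associated with whole body vibration exercise, which will be reported", alongside VAS pain and the ODI.

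On analysis, the Statistical analysis section plans a two-way repeated measures ANOVA (group by time) and says that, for subjects lost to follow-up, "an intention-to-treat analysis will be conducted". The Abstract makes the same commitment for participants who withdraw.

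**The concern.** A patient may stop a treatment and still be measured. This rule does not draw that line: what the patient leaves is the study. It also applies unevenly. A WBV patient whose back flares up, with the flare-up attributed to vibration, meets the third item. A control patient with a similar flare-up from the same squat or back extension does not, and would have to leave by request or for serious disease, routes that are open to both arms.

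The rule can therefore create missing VAS and ODI values in one arm, in patients selected for having reacted badly to the treatment under test. If those patients would have scored worse than the rest of their arm, the observed WBV mean is too favourable. The third aim of the trial is to determine the adverse effects of WBV, and patients with such effects are the ones whose follow-up may be cut short.

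**Working it through.** **Step 1: who can meet the rule.** Request and serious disease can arise in either arm. The third item needs an effect related to vibration exercise, and controls receive no vibration. The asymmetry follows from setting the withdrawal list beside the description of the control group.

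**Step 2: what is lost.** Assessments are at baseline, 3 months and 6 months. A patient who leaves the study before the 3-month visit has only the baseline value. A repeated measures ANOVA in its standard form uses only subjects with all time points, so that patient drops out of the comparison unless values are imputed.

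**Step 3: how much it could matter.** The plan has no figure to reproduce: it gives 120 patients without an SD, effect size, power or expected withdrawal rate. The following is illustration only.

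Inputs from the article:
- 120 patients allocated 1:1, so 60 per arm.
- Significance level 0.05; two-sided is assumed, since the article does not say.

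Assumptions, none from the article:
- no true difference between arms;
- a share p of the WBV arm withdrawn under the third item, from 3% to 20% (about 2 to 12 of 60);
- withdrawn patients would score D SD worse than the WBV patients who remain, with D from 0.5 to 1.5;
- no outcome-related loss in the control arm;
- no adjustment for baseline.

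Formulas, in SD units:
- bias = p × D;
- SE = √(1/60 + 1/(60(1 − p)));
- type I error = 1 − Φ(1.96 − bias/SE) + Φ(−1.96 − bias/SE).

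Worked case, p = 10% and D = 1: 54 WBV patients remain; bias = 0.10 × 1 = 0.10; SE = √(1/60 + 1/54) = 0.188; bias/SE = 0.533; type I error = 0.083.

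| Withdrawn from WBV arm | D = 0.5 SD | D = 1.0 SD | D = 1.5 SD |
|---|---|---|---|
| 3% | 0.051 | 0.053 | 0.057 |
| 5% | 0.052 | 0.058 | 0.069 |
| 10% | 0.058 | 0.083 | 0.126 |
| 15% | 0.068 | 0.124 | 0.219 |
| 20% | 0.081 | 0.178 | 0.341 |

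The bias runs from 0.03 × 0.5 = 0.015 SD to 0.20 × 1.5 = 0.30 SD. For scale, 60 per arm detects (1.96 + 0.84) × √(2/60) = 0.51 SD with 80% power.

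**Step 4: sensitivity to the set-up.** If D is instead the gap to the average of the whole WBV arm, the bias is pD/(1 − p), for example 0.10/0.90 = 0.11 SD in the worked case. A baseline-adjusted analysis with a correlation of 0.5 multiplies the SE by √(1 − 0.5²) = 0.866 and gives 0.094 in the worked case, but that is not the planned analysis.

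**Step 5: after the change.** If everyone randomized is measured at 3 and 6 months whatever happens to the exercise, p is 0 for this route, the bias from it is 0 and the type I error is 0.05.

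**The case against.** The strongest reply has four parts.

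- **Withdrawal is not automatic.** The wording is "will be allowed or be asked to withdraw from the study if". A reader might infer that every patient with a vibration-related effect is removed; the text does not say so. This stands. Even so, being asked to leave is an action directed by the protocol, so the route to missing data is real.
- **The direction is not proven.** A reader might infer that the worst outcomes are taken out of the WBV arm. A vibration-related effect need not be back pain, and nothing shows that these patients would have the worst VAS or ODI. Controls who do badly can leave by request, which could offset part of the bias. This stands: favouring WBV is the likely direction, no more.
- **Intention-to-treat is already planned.** A reader might infer that the rule contradicts it. It does not: the authors foresaw withdrawals and named a response, and the handling of missing values may be set out in an analysis plan that is not shown. The rule does weaken that analysis, because imputation would have to fill gaps that are specific to one arm and probably informative.
- **The article is condensed.** The section does not say that assessments end at withdrawal, and the full protocol may provide for later contact. The event that prompts withdrawal is known and can be reported, so what is at risk is its later course, not its count. This narrows the point. It does not remove it, because the published rule itself makes leaving the study the response.

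**Conclusion.** The concern holds in a limited form. The rule as written makes a vibration-related adverse effect a ground for leaving the study, and only one arm can meet it. A patient who leaves this way during the intervention, and is not assessed afterwards, has no post-baseline VAS or ODI, and intention-to-treat cannot replace those values.

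The size is unknown. With few withdrawals the effect is negligible: at 3% to 5% withdrawn and an excess of up to 1 SD, the type I error stays below 0.06. It becomes serious only if withdrawals are common and clearly worse off, reaching 0.18 at 20% and 1 SD, and 0.34 at 20% and 1.5 SD. These figures rest on assumed rates and excesses, no offsetting loss among controls, and a comparison limited to patients with data.

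The documents do not support saying that withdrawal is automatic, that the worst outcomes are certainly removed, that intention-to-treat is contradicted, or that the adverse events themselves go unrecorded.

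**What to change.** Amend Withdrawal criteria and management so that stopping the assigned exercise is separate from leaving the study. Suggested wording: *Participants in either group who stop the assigned exercise remain in the study in the group to which they were randomized. VAS, ODI and adverse events, the latter by the same definition in both groups, are still collected at 3 and 6 months unless the participant withdraws consent to follow-up or is medically unable to attend.*

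When exercise stops remains the investigators' clinical decision and is not changed by this wording.

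The cost is a short amendment and some extra effort to keep contact with participants who have stopped exercising. The 3- and 6-month visits already exist, and VAS and ODI are questionnaires. Recruitment is already underway according to Trial status, and outcomes that are not collected on time cannot be recovered later, so the change should be made promptly.
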